**Fig. 3 Fig3:**
[figure not shown]
The SPIRIT figure

Block randomization with a block size of about 20 using a restricted shuffled approach will be used to ensure an even distribution of individuals among the study arms. The randomized block is based on the time sequence of participant recruitment. Whenever an individual is being recruited, a consecutively coded number (i.e. participant code number) will be assigned to him/her according to the time sequence of recruitment. After the baseline data collection, the first 20 individuals being recruited (e.g. participant code numbers 1–20) will be evenly randomized to the study arms in a block. A computer-generated random sequence determines the group assignment of these 20 individuals. Twenty paper cards labelled with “exercise” or “control,” with each placed in a single sealed opaque envelop, will be arranged in an order to represent the generated sequence. These envelopes will be numbered consecutively according to this specified order and distributed to the 20 participants according to the participant code sequence. The RA2 will open the envelope for the individuals; with the information on the paper cards represent their group status. The same method will be used to randomize the subsequently recruited participants. Each block of individuals will have an independent computer-generated random sequence to determine the group assignment.

The participants will receive the assigned intervention within two weeks of baseline measure. They will not be informed about whether their received intervention is the tested one. For all individuals, the author ([name]) will measure perceived treatment credibility at the fifth week of training. This timeframe allows sufficient exposure to treatment before reporting expectations [2]. Another RA (RA3), who is blinded to the participants’ group status, will measure the mediating and outcome variables upon completion of the study intervention for all the study individuals.

After the post-test data collection, the RA2 will interview 30 participants from the exercise arm who have reported different levels of change in the sleep quality. An interview guide with board open-ended questions as outlined in Table 2 will guide the exploration on the individuals’ perception of the exercise training, with particular focus on how and why they perceive exercise therapy would or would not influence sleep and perceived acceptability of this lifestyle intervention. Probes corresponding to the hypothesized mediating variables will be used so that the qualitative findings can enhance the interpretation of the quantitative findings. The interview will be audio-taped to facilitate data analysis.

**Table 2 Tab2:** Interview guide for the qualitative interview

Questions	Probe
1. How do you feel about the 16-week exercise training?	Acceptability and tolerance
2. How has your sleep quality and pattern changed while you were participating in the 16-week exercise training?	- Sleep latency - Sleep duration - Number and duration of nocturnal awakenings - Early morning awakening - Daytime sleepiness - Feeling refreshed in the morning
3. How is your current sleep pattern and quality different from the situation before you participated in the 16-week exercise training?	
4. You have mentioned that you have improved sleep after participating in the 16-week exercise training. What are the possible reasons leading to such changes? OR You have mentioned that your sleep quality and pattern remain the same after participating in the exercise training. Why is that? What are the possible reasons?	- Physical fitness - Mood change - Perception on sleep disturbance - Perceived effectiveness of exercise training
5. Will you recommend the 16-week exercise training to your friends or family who have disturbed sleep? Why?	
6. Will you consider doing regular moderate-intensity exercise in the future? Why?	

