### Issues of compliance

A previous study examining the effects of exercise therapy among Hong Kong older adults reported high compliance rate of around 80% for these two study interventions [22]. Various strategies, which are based on social cognitive theory and health belief model, will be used to optimize the individuals’ compliance. Table 1 outlines details of these strategies for promoting group cohesion, increasing perceived self-efficacy, and providing emotional and tangible incentives. The first author will provide a one-day training to the RA1 and RA2 on how to incorporate these strategies to the interventions. As the intervener–participant interaction may influence the treatment effect and is difficult to equalize between study arms, a 7-point semantic differential scale will be used to measure the individuals’ perceptions of the characters of the interveners including “friendliness,” “caring,” “sincerity,” “cheerfulness,” and “considerateness” during the post-test data collection. This captures any possible experimenter effect for statistical adjustment if necessary.

**Table 1 Tab1:** Strategies to optimize compliance to the study interventions

Strategies	Actions
Promoting group cohesion	- Group affiliation: Chinese titles will be assigned to exercise and health education program. Each class and participant will have an arm badge to signify their group identity. - Ice-breaking: Conduct two ice-breaking activities at the first training session to introduce the perception that they are “on the same boat” and have similar sleeping problems. - Goal-setting: The intervener facilitates the group to set the goal of achieving mean attendance rate of not less than 85% for each 2 weeks. The bi-weekly attendance rates will be presented graphically to the group and posted in the training room. - Group socialization: The intervener will foster communication between the participants to increase group socialization at the beginning and at the end of each training session.
Improving perceived self-efficacy	- Effective teaching: A step-by-step approach will be used to equip the individuals with the skills in conducting the intervention. The pace of teaching will be adjusted according to the participants’ learning needs. Clear instruction, demonstration, and return demonstration will be used as core teaching strategies. - Positive evaluation: The interveners will give positive evaluative feedback and encouragement to the individuals in each session.

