#### Expectation on treatment credibility

Expectation on treatment credibility refers to the respondent’s expectation of the sleep-promoting effect of the received intervention. A four-item questionnaire is used, which rates the (1) reasonableness of treatment, (2) opinion of the therapist, (3) expectation for improvement, and (4) likelihood to recommend the treatment to others, on a 10-point scale, with a higher score indicating a better expectation [28].

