### Data processing and analysis

Data will be double-entered for validation and analyzed on an intention-to-treat (ITT) basis. Skewed variables will be transformed before being subjected to analyses. Baseline characteristics between the two arms of participants will be compared using t test, chi-square test or Fisher’s exact test, as appropriate. Mixed effects models will be used to compare the differential changes on the primary (sleep pattern and quality) and secondary (physical fitness and mood status) outcomes across the baseline and post-test (T2) between the two study arms, with adjustment for the potential control variables (i.e. expected treatment credibility, demographic and health profile) which are statistically non-equivalent at baseline (*p* < 0.25). In particular, a dummy variable (group) will be assigned to represent the exercise training group (i.e. treatment group) with the health education group (i.e. control group) as reference, and another dummy variable (time) will be set to indicate the time points (1 = post-test, 0 = pre-test) in the mixed effects model. To accurately identify the effects of the exercise training, an interaction term group × time will also be included in the model to assess the difference in the change of each outcome across the pre-test and post-test period (i.e. pre-post change) between the two study groups. The statistical significance of the model coefficients, including the interaction term, will be assessed by Wald test. The strengths of mixed effects model lie in accounting for intra-correlation between repeatedly measured data and accommodating missing data caused by dropout, provided the data are missing at random [26]. This method is most suitable for ITT analysis without the need for missing data imputation. All analysis will be conducted by using SAS release 9.3 (SAS Institute Inc, Cary, NC) at a 5% level of significance. Depending on the data distribution, the mixed effects modeling will be performed using the PROC MIXED or NLMIXED.

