Path analysis is used to examine the mediating roles of physical fitness and mood status on the effect of exercise training on sleep pattern and quality with adjustment for the above control variables. Based on our hypothesized mediation model (Fig. 1), a baseline path model using the baseline data will be built first. To which path model with the same structure for T2 is added and linked by intra-correlations among the same variables. The final mediation model will then consist of two clusters (corresponding to the two time points) and are linked by the intra-correlations. The equality of a specific path coefficient in the two clusters can be assessed by imposing equality constraint on the coefficient and tested using a nested goodness-of-fit test [27]. The mediation effects of physical fitness and mood status on the effect of exercise training on sleep pattern and quality will be assessed through the significance of the corresponding products of indirect path coefficients from exercise training to sleep pattern and quality, respectively [28]. In view of the possibility of violation of normality assumption, a bootstrapping approach [28], instead of the conventional multivariate delta method, will be used to estimate the standard errors and the confidence intervals of the product terms (mediation effects). Furthermore, the effect of exercise training (as compared to control) on the change of the path coefficients to the sleep pattern and quality outcomes directly or by way through the mediators (physical fitness and mood status) over time can be assessed using the three-way interactions approach [27]. The path analyses and the bootstrapping will be performed using Mplus Version 6 and the parameters will be estimated by mean and variance adjusted weighted least square method (WLSMV). The bootstrapping estimations of the standard errors and confidence intervals will be performed using bias-corrected bootstrapping method with 10,000 replications [28]. The overall fit of the path models is assessed using comparative fit index (CFI), root mean square error of approximation (RMSEA), and standardized root mean square residual (SRMR), with CFI > 0.95, RMSEA < 0.06, and SRMR < 0.08, indicating a good data-model fit [27].

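### Expected treatment credibility is to be screened as a baseline control variable but is measured at week 5; adjusting for it can bias the path model and drop participants from the ITT analysis

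*Protocol article*

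**What the plan says.** All references are to the Protocol article.

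- **Definition** (Expectation on treatment credibility): the respondent's "expectation of the sleep-promoting effect of the received intervention", on four items that include the opinion of the therapist. The Outcome variables section counts it among potential confounders.
- **Timing** (Method of randomization and data collection procedure): an investigator "will measure perceived treatment credibility at the fifth week of training". The reason given is: "This timeframe allows sufficient exposure to treatment before reporting expectations". The baseline data listed in that section are the fitness test, demographic and health profile, PSQI, POMS-SF and actiwatch recording. Credibility is not among them.
- **Outcome models** (Data processing and analysis): mixed models with group, time and group × time, "with adjustment for the potential control variables (i.e. expected treatment credibility, demographic and health profile) which are statistically non-equivalent at baseline", with a threshold of p < 0.25. The same section plans ITT analysis and says the mixed model needs no imputation.
- **Path model** (same section): the roles of fitness and mood are examined "on the effect of exercise training on sleep pattern and quality with adjustment for the above control variables".
- **Intervener ratings** (Issues of compliance): participants rate their intervener at post-test. "This captures any possible experimenter effect for statistical adjustment if necessary". No model is named.

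**The concern.** A variable first recorded five weeks into the assigned programme, and defined by that programme, has no baseline value that can be non-equivalent. The screening rule cannot be applied to it as written. Applied to the week-5 score instead, it selects credibility precisely when the two programmes have produced different expectations. That difference may be a consequence of allocation, which randomisation gives no reason to remove.

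Two things are at stake. First, where credibility lies on the route from exercise to sleep, conditioning on it in a model of the post-test outcome removes that part of the effect. Where it shares unmeasured causes with sleep or mood, conditioning can also introduce bias in either direction. Second, a mixed model tolerates missing outcomes but not missing covariates. A participant without a week-5 score is dropped entirely, baseline record included.

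The intervener ratings are also post-randomisation. In addition, RA1 delivers only exercise and RA2 only education, so an intervener effect cannot be separated from the treatment effect.

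**Working it through.** **Inputs from the protocol.** 224 randomised (112 per arm), effect size 0.4, 80% power, 5% level (two-sided assumed), 10% attrition.

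**The plan's own figures.** 2 × ((1.960 + 0.842)/0.4)² = 98.1 per arm. Averaging 10% attrition over two waves (mean retention 0.95, an assumption about how the program works) gives 98.1/0.95 = 103.3, hence the stated 104. Also 112 × 0.9 = 100.8, the stated 100 per arm. The point does not depend on these figures.

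**1. How often would the screen select week-5 credibility?** For a true arm difference d (in SD) and n per arm, the chance of p < 0.25 is 1 − Φ(1.150 − d√(n/2)) + Φ(−1.150 − d√(n/2)). With n from 100.8 to 112:

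- d = 0: 25%
- d = 0.2: 61–64%
- d = 0.4: 95–97%

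**2. Effect left after adjusting a model of the post-test outcome.** Let a be the arm effect on credibility (SD) and b the effect of credibility on the outcome (SD per SD). With no unmeasured common causes, the adjusted effect is 0.40 − a × b. Neither a nor b is in the protocol, so a range is shown. In brackets is the power of a two-mean comparison with 100 per arm, Φ(d√50 − 1.960).

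| a | b = 0.1 | b = 0.2 | b = 0.3 |
|---|---|---|---|
| 0.2 | 0.38 (77%) | 0.36 (72%) | 0.34 (67%) |
| 0.4 | 0.36 (72%) | 0.32 (62%) | 0.28 (51%) |
| 0.5 | 0.35 (70%) | 0.30 (56%) | 0.25 (42%) |

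The loss runs from 0.02/0.40 = 5% to 0.15/0.40 = 37.5%. The powers illustrate scale; they are not powers for a path coefficient.

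**3. Does this carry over to group × time?** In complete data the group × time estimate is the arm difference in mean post-minus-pre change. A covariate that is constant over time and has no time interaction cancels from each person's change. A simulation (400 runs, 112 per arm, a = 0.5, b = 0.3, 10% attrition with half before week 5) gave these mean estimates, with Monte Carlo standard errors of 0.006–0.007:

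| Model | Estimate |
|---|---|
| Mixed model, no credibility | 0.385 |
| Mixed model, credibility as main effect, early leavers deleted | 0.384 |
| Mixed model, credibility × time added | 0.233 |
| ANCOVA on completers, no credibility | 0.392 |
| ANCOVA on completers, credibility added | 0.238 |

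In complete data, adding the main effect changed the estimate by 0.000. The drops of about 0.15 in the other two settings match a × b = 0.15. The path model itself was not simulated. The ANCOVA rows stand in for it because both condition the post-test outcome on credibility.

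**4. Participants lost.** At 10% attrition, with share s leaving before week 5, the model with credibility keeps 224 × (1 − 0.1s): 224 for s = 0, about 213 for s = 0.5, about 202 for s = 1. The loss is 0 to about 22. With the post-test rating as covariate it keeps 224 × 0.9 = 201.6, about 202. Without these covariates all 224 can stay in through their baseline records.

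**The case against.** The strongest reply is that the primary analysis is hardly touched. The protocol specifies group, time and group × time with covariates added, and names no covariate × time term and no ANCOVA. On that reading, step 3 shows the treatment estimate does not move. **This stands.** A reader might infer that adjustment strips more than a third of the primary effect. The documents do not support that: the figure needs the least favourable corner of the assumed grid and a type of adjustment that, among the planned analyses, only the path model clearly uses, and the path model serves a secondary aim. The text does, however, leave open whether covariates interact with time. It also allows NLMIXED, where the linear result need not hold.

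Other points on that side:

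- *Adjustment is conditional.* True: it depends on the p < 0.25 screen, and read literally a variable without a baseline value could never qualify. But the protocol names credibility first in its list of control variables, so analysts are likely to apply the screen to the week-5 score.
- *Missing scores may be few.* Credibility is planned for all participants, so leaving the classes need not mean a missing value. This is why the loss is given as 0 to about 22. Those without a post-test also carry limited information on group × time.
- *The intervener ratings are not in the path model.* Correct. A reader might infer otherwise, but the control-variable list is closed and omits them, and Issues of compliance names no model. Individual ratings also vary within arm, so they are not collinear with group; it is intervener identity that coincides with arm.
- *There is a precedent.* The Background reports an earlier trial whose benefit was found after adjustment for expected credibility. That supports a labelled additional analysis of a different quantity, but not credibility as a baseline control variable.

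**Conclusion.** The point holds in a limited form. The protocol treats as a baseline control variable something its text measures only at week 5, about the intervention received. The SPIRIT figure (Fig. 3) could not be read for this review and should be checked for any earlier measurement.

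If the screen selects credibility:

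- **Path model, or any ANCOVA-type or covariate × time adjustment:** a total effect of 0.40 becomes 0.38 to 0.25 under the assumed ranges of a and b. The direction is not assured if credibility shares unmeasured causes with sleep.
- **Linear mixed model with a time-constant main effect:** group × time is essentially unchanged. The harm is the deletion of 0 to about 22 of 224 participants, which conflicts with the stated ITT analysis. No bias from that deletion has been quantified.

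The open-ended adjustment for intervener ratings is a separate, smaller defect. It is tied to no model, cannot isolate an experimenter effect, and would restrict the analysis to about 202 of 224. The documents do not support saying that the models will certainly adjust for either variable, or that the primary group × time effect is necessarily reduced.

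**What to change.** - In Data processing and analysis, remove expected treatment credibility from the control variables for both the mixed models and the path model. State that only variables measured before randomisation may be covariates in the primary and mediation models.
- In Outcome variables, stop describing week-5 credibility as a potential confounder.
- In Issues of compliance, replace the provision for adjustment with a commitment to report intervener ratings by arm.
- Report credibility by arm. Use credibility and the ratings only in analyses labelled exploratory or sensitivity, with the number of participants included and a note that these estimate something other than the total effect of allocation.

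The cost is wording only, made before analysis; all the data are still collected. If expectation is wanted as a covariate, it would have to be measured before randomisation. With recruitment already under way, that could cover only later participants.

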### Data processing and analysis

Data will be double-entered for validation and analyzed on an intention-to-treat (ITT) basis. Skewed variables will be transformed before being subjected to analyses. Baseline characteristics between the two arms of participants will be compared using t test, chi-square test or Fisher’s exact test, as appropriate. Mixed effects models will be used to compare the differential changes on the primary (sleep pattern and quality) and secondary (physical fitness and mood status) outcomes across the baseline and post-test (T2) between the two study arms, with adjustment for the potential control variables (i.e. expected treatment credibility, demographic and health profile) which are statistically non-equivalent at baseline (*p* < 0.25). In particular, a dummy variable (group) will be assigned to represent the exercise training group (i.e. treatment group) with the health education group (i.e. control group) as reference, and another dummy variable (time) will be set to indicate the time points (1 = post-test, 0 = pre-test) in the mixed effects model. To accurately identify the effects of the exercise training, an interaction term group × time will also be included in the model to assess the difference in the change of each outcome across the pre-test and post-test period (i.e. pre-post change) between the two study groups. The statistical significance of the model coefficients, including the interaction term, will be assessed by Wald test. The strengths of mixed effects model lie in accounting for intra-correlation between repeatedly measured data and accommodating missing data caused by dropout, provided the data are missing at random [26]. This method is most suitable for ITT analysis without the need for missing data imputation. All analysis will be conducted by using SAS release 9.3 (SAS Institute Inc, Cary, NC) at a 5% level of significance. Depending on the data distribution, the mixed effects modeling will be performed using the PROC MIXED or NLMIXED.

Path analysis is used to examine the mediating roles of physical fitness and mood status on the effect of exercise training on sleep pattern and quality with adjustment for the above control variables. Based on our hypothesized mediation model (Fig. 1), a baseline path model using the baseline data will be built first. To which path model with the same structure for T2 is added and linked by intra-correlations among the same variables. The final mediation model will then consist of two clusters (corresponding to the two time points) and are linked by the intra-correlations. The equality of a specific path coefficient in the two clusters can be assessed by imposing equality constraint on the coefficient and tested using a nested goodness-of-fit test [27]. The mediation effects of physical fitness and mood status on the effect of exercise training on sleep pattern and quality will be assessed through the significance of the corresponding products of indirect path coefficients from exercise training to sleep pattern and quality, respectively [28]. In view of the possibility of violation of normality assumption, a bootstrapping approach [28], instead of the conventional multivariate delta method, will be used to estimate the standard errors and the confidence intervals of the product terms (mediation effects). Furthermore, the effect of exercise training (as compared to control) on the change of the path coefficients to the sleep pattern and quality outcomes directly or by way through the mediators (physical fitness and mood status) over time can be assessed using the three-way interactions approach [27]. The path analyses and the bootstrapping will be performed using Mplus Version 6 and the parameters will be estimated by mean and variance adjusted weighted least square method (WLSMV). The bootstrapping estimations of the standard errors and confidence intervals will be performed using bias-corrected bootstrapping method with 10,000 replications [28]. The overall fit of the path models is assessed using comparative fit index (CFI), root mean square error of approximation (RMSEA), and standardized root mean square residual (SRMR), with CFI > 0.95, RMSEA < 0.06, and SRMR < 0.08, indicating a good data-model fit [27].

For the qualitative data, the audio-taped interview will be transcribed verbatim by the RA2. The authors will carefully review the transcribed content. Inductive thematic analysis will be used to code the data on the overall perception and perceived acceptability of exercise program. For the findings about why and how exercise influences or not influences sleep, a priori coding framework based on the hypothesized mediating process of exercise on sleep will be used to obtain the data clusters. Inductive thematic analysis will also be used to code the data which does not represented by the model construct. The coded units will be sorted into categories and subcategories and analyzed for recurrent themes and pattern. Within-case and across-case analyses in each group of participants with a similar change in the PSQI score will be conducted and followed by cross-group analysis. Data credibility will be further maintained by conducting an audit trail. The emerged categories will be reviewed for resonance with the quantitative findings. The qualitative findings serve a complementary purpose in concluding the effect, the mediating process, and the acceptability of exercise on sleep among older adults.

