#### Demographic and health profiles

Participants’ demographic and health profile including age, gender, education level, marital status, living conditions, lifestyle, and medical and drug history will be collated.

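### Adjustment covariates are picked by baseline significance tests (p < 0.25), that is, by chance imbalance and not by prognostic value, and one candidate has no baseline value to test

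*Protocol article*

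**What the plan says.** All of this is in the protocol article.

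- *Data processing and analysis* plans significance tests of baseline balance: "Baseline characteristics between the two arms of participants will be compared using t test, chi-square test" or Fisher's exact test.
- The same section takes as candidates the "potential control variables (i.e. expected treatment credibility, demographic and health profile" and adjusts for those "which are statistically non-equivalent at baseline", with p < 0.25 as the threshold. This applies to both primary and secondary outcomes. No covariate is fixed in advance, and prognostic strength plays no part.
- *Demographic and health profiles* lists the candidates: "age, gender, education level, marital status, living conditions, lifestyle, and medical and drug history".
- The treatment effect is the interaction: "an interaction term group × time will also be included in the model to assess the difference in the change of each outcome". Group, time and group × time are the only terms described. The form in which covariates enter is not given.
- The path analysis, later in *Data processing and analysis*, adjusts for the same control variables.
- *Method of randomization and data collection procedure* describes a computer-generated sequence in sealed opaque envelopes. It places the credibility measurement in week 5 of the intervention.
- *Study settings and participants* assumes for the sample size that randomisation makes the arms equal at baseline, and allows for 10% attrition.

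**The concern.** Under concealed randomisation, a baseline p-value for a pre-randomisation variable measures only how the allocation happened to fall. A strong predictor of sleep with p = 0.30 is left out, while an irrelevant variable with p = 0.20 goes in. The content of the primary model is unknown until baseline data have been compared by arm.

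Three things are at stake. Precision that good predictors could give is left to luck. The adjustment may do nothing for the coefficient that carries the treatment effect, or, once there is dropout, may move it according to which covariates were selected. And for treatment credibility the rule cannot be applied as written, because the variable does not exist at baseline.

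**Working it through.** The plan gives no figure on this point to reproduce. The check has four parts.

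**1. How often chance selects a covariate.** *Demographic and health profiles* gives 7 items if medical and drug history count as one, 8 if they are separate, and 9 if one broad heading yields a second variable. With correct randomisation, each test falls below 0.25 with probability 0.25. Independent tests are assumed. For k candidates, the expected number selected is 0.25k and P(at least one) = 1 − 0.75^k.

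| k | Expected number | P(at least one) |
|---|---|---|
| 7 | 1.75 | 1 − 0.75^7 = 0.87 |
| 8 | 2.00 | 1 − 0.75^8 = 0.90 |
| 9 | 2.25 | 1 − 0.75^9 = 0.92 |

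Conversely, any given predictor, however strong, is left out with probability 0.75.

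**2. What a main-effect covariate does to group × time.** Take Y(t) = b0 + b1·group + b2·t + b3·group·t + c·X + u + e(t), with X fixed over time. Subtracting the two time points gives Y(1) − Y(0) = b2 + b3·group + e(1) − e(0), so X drops out. With both measurements on everyone, b3 is the difference in mean change whether or not X is in the model.

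A simulation checked this and then added dropout. It assumed a random-intercept model, 112 per arm, pre-post correlation 0.5, an effect of −0.4 SD, a covariate explaining 20% of outcome variance, and 40 replicates per scenario.

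| Post-test dropout | Mean shift in group × time on adding X (SD) | Largest shift (SD) |
|---|---|---|
| None | 0 | 5e-15 (rounding error) |
| 10%, at random | 0.007 | 0.026 |
| 10% nominal, depending on X in opposite directions by arm | 0.055 | 0.089 |
| 20% nominal, same mechanism | 0.088 | 0.145 |

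Against the target of 0.4, random 10% dropout shifts the estimate by 0.007/0.4 = 2% on average. The strongly differential 10% case, which is an assumption and not something the protocol predicts, shifts it by 0.055/0.4 = 14%. The standard error hardly moves: it changes by under 0.00001 with complete data, and is 0.139 with and without X at 10% random dropout.

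**3. What a pre-specified baseline-adjusted analysis would gain.** With outcome variance σ² and pre-post correlation ρ, the per-person variance is 2σ²(1 − ρ) for the change contrast and σ²(1 − ρ²) for ANCOVA. The ratio is (1 − ρ²)/[2(1 − ρ)] = (1 + ρ)/2, which gives 0.65, 0.75 and 0.85 at ρ = 0.3, 0.5 and 0.7. The article states no correlation, so this range is assumed.

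**4. Treatment credibility.** It is named as a candidate to be screened for baseline non-equivalence, but is measured in week 5, after randomisation and after exposure to the assigned programme. There is no baseline value to test. The argument that differences are chance does not apply to it either, because the programme received may itself change it.

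**The case against.** The strongest reply is that the candidates and the threshold are stated beforehand, so this is a fixed rule and not ad hoc selection, and that its effect on the primary estimate is small. Both parts stand. But a fixed rule that selects on chance imbalance still leaves the model's content to chance, and the small effect also means that the adjustment achieves little.

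A reader might infer that adjustment can never alter the group × time estimate. The documents do not support that. The result needs time-fixed covariates entered as main effects, a linear model and complete data. The article does not state the form of entry, expects 10% attrition, and allows a non-linear route: "the mixed effects modeling will be performed using the PROC MIXED or NLMIXED". The two limbs of the point also apply in different settings: with complete data the selection is inert, and with dropout it matters, usually slightly.

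A reader might also infer that the error rate of the primary test is inflated. No calculation shows this. Nor is it right that baseline imbalance goes uncorrected: the pre-post contrast already removes baseline level differences in the outcome, and only covariate effects on change would remain.

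On credibility, one could say that the baseline condition was meant only for demographic and health items. The sentence does not read that way, and a week-5 variable would remain post-randomisation.

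**Conclusion.** The concern holds in a limited form. The p < 0.25 rule is stated text, not a detail left to an analysis plan. It selects pre-randomisation covariates by chance imbalance and without regard to prognosis: about two are expected by chance, and at least one with probability 87% to 92%, assuming 7 to 9 candidates and independent tests. For the group × time estimate, main-effect adjustment changes nothing with complete data in a linear model. At 10% random dropout it shifts the estimate by 0.007 SD on average (maximum 0.026) under the simulated conditions, and by more only if dropout is strongly differential. Inclusion of week-5 credibility contradicts the rule's own baseline condition.

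Material harm to the primary test is not shown. What is shown is that the rule does not do the work of covariate adjustment, while a better-specified model would use data already being collected.

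**What to change.** - Delete the p < 0.25 rule and the baseline significance tests. Describe baseline by summary statistics by arm.
- Name a few pre-randomisation prognostic covariates in advance, for example age and gender. Use them whatever their imbalance, and let them act on the post-test outcome (as covariates in ANCOVA, or with covariate × time terms in the mixed model).
- Take account of the baseline outcome through ANCOVA or a mixed model with a common baseline mean. Do not add it as a covariate × time term, because it is already a response in the planned model.
- Keep week-5 credibility out of the primary model. If it is reported, label it a post-randomisation measure.
- State the same covariate set for the path analysis.

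The cost is a re-worded primary model and a few degrees of freedom out of about 200 completers (112 × 0.9 ≈ 100 per arm). No new data are needed, and the article reports recruitment as still ongoing.
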